### Outcome measures

The outcome measures for the primary and secondary objectives are outlined in table 1.

**Table 1 T1:** Study objectives and outcome measures

Objective	Outcome measure
Primary: Determine the potential effect of the LCP on discharge	The measured difference between standard care and the three LCP-based options described under AI model for: No and percentage of cancer patients discharged (straight after assessment of the baseline scan). No and percentage of benign-nodule patients discharged (straight after assessment of the baseline scan).
Secondary: Determine the potential effect of the LCP on possible adherence to clinical guidelines	The measured difference between standard care and the three LCP-based options described under AI model: No and percentage of patients for whom a validated risk model (Brock or LCP) is used to guide the next clinical management step (ie, counting the instances where Brock is not used or where LCP is not possible to compute, or it is ignored).
Secondary: Determine the potential effect of the LCP on overall clinical management, as well as scan and procedure utilisation	No and percentage of cancer patients for whom there would have been a change in clinical management according to each of the three LCP-based options described under AI model compared with actual care (correctly for more aggressive management and incorrectly for less aggressive management). No and percentage of benign-nodule patients for whom there would have been a change in clinical management according to each of the three LCP-based options described under AI model compared with actual care (incorrectly by more aggressive management and correctly for less aggressive management). The measured difference between standard care and the three LCP-based options described under AI model for: No and percentage of CT scans and PET/CT scans performed on benign-nodule patients. No and percentage of non-surgical biopsies performed on benign-nodule patients. No and percentage of surgical excisions on benign-nodule patients.

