### Statistical analysis

#### Sample size

For calculations relating to the primary objectives of a measured difference between standard care and LCP for:

Number and percentage of cancer patients discharged: results from thresholds defined for discharge in a previous study are used.^7^ Based on previous data within the cancer group, assuming for the discordant pairs that the Brock model threshold (representing the standard of care) identified 0.4% of cancers for which the LCP threshold would have recommended discharge, and the LCP threshold correctly identified 2.6% of cancers for which the Brock model threshold would have recommended discharge, then using McNemar’s test with 90% power and a significance level of 0.05, 659 participants would be needed. However, with a sample size of 2000, there is 90% power to detect a difference between the methods if the percentages were as small as 1.0% and 2.3%, respectively.Number and percentage of benign-nodule patients discharged: again, results from thresholds defined for discharge in a previous study are used.^7^ Based on previous data within the benign group, assuming for the discordant pairs that 17.0% of benign nodules are recommended for discharge by the LCP threshold but not by the Brock model threshold. In comparison, 13.5% are recommended for discharge by the Brock model threshold but not by the LCP threshold; there is 80% power to detect a significant difference between the two tests with 2026 individuals using McNemar’s test. This equates to an OR of 1.26

Sample size calculations were performed using R statistical software (V.4.1.2; R Foundation for Statistical Computing, Vienna, Austria).

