#### Statistical analysis

Statisticians will carry out all analyses. For each outcome measure, the following will be reported:

The number of participants included in the analysis, stratified by the relevant group.Mean or median (SD or IQR) for continuous outcomes, and numbers and proportions (percentage) for binary outcomes.An effect size (OR) with a 95% CI.A two-sided p value.

For both primary objectives, measured differences between standard care and the LCP options for patients with cancer diagnosed and benign-nodule patients discharged will be analysed using conditional logistic regression. Statistical significance will be assessed with a Wald test. Secondary outcomes will be described and analysed according to their distribution. All outcomes will have an exact p value provided for them so the reader can access the data for significance level, so correction for multiple testing should not be needed.

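### For the cancer-discharge primary outcome, the prescribed Wald test is unsuitable because discordant cancers will be sparse; an exact or mid-p McNemar test should replace it

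*Protocol article*

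**What the plan says.** The Statistical analysis section of the protocol article prescribes one analysis for both primary outcomes: the differences between standard care and the LCP options "will be analysed using conditional logistic regression. Statistical significance will be assessed with a Wald test". For each outcome it also promises numbers and percentages, "An effect size (OR) with a 95% CI", and a two-sided p-value.

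Table 1 defines the cancer outcome among cancer patients only: "No and percentage of cancer patients discharged (straight after assessment of the baseline scan").

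The Sample size section bases power on McNemar's test. For cancers it assumes that the Brock threshold "identified 0.4% of cancers for which the LCP threshold would have recommended discharge" and that "the LCP threshold correctly identified 2.6% of cancers for which the Brock model threshold would have recommended discharge". From these rates it concludes, for McNemar's "test with 90% power and a significance level of 0.05, 659 participants would be needed". For benign nodules it assumes that "17.0% of benign nodules are recommended for discharge by the LCP threshold but not by the Brock model threshold", against 13.5% the other way, and states 80% power with 2026 individuals.

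**The concern.** With paired yes/no decisions, the conditional odds ratio and its Wald test depend only on the two discordant counts. The Wald statistic needs both counts to be above zero and is unreliable when either is very small. If every discordant cancer falls on one side, the estimate runs to zero or infinity, its standard error grows without limit, and the p-value drifts towards 1 however one-sided the data are.

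At stake is the safety half of the primary objective. A result in which the LCP discharged several cancers that standard care kept, with none the other way, would be reported as non-significant with an unusable confidence interval. So would the mirror-image result in its favour.

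**Working it through.** **Inputs.** From the Sample size section: discordance among cancers of 0.4% and 2.6%, 659 participants, 90% power, alpha 0.05; discordance among benign nodules of 13.5% and 17.0%, 2026 individuals, 80% power. From Statistical analysis: two-sided p-values. From Design and setting: 2000 patients in total. The article gives no cancer prevalence; its Abstract says only that a small share of nodules are cancers. I assume 5% to 15%, that is 100 to 300 cancers, and also show larger numbers.

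**Step 1: reproduce the plan's figure.** With total discordance pd = 0.030 and difference d = 0.022, the paired-proportions formula is n = (1.96·√pd + 1.2816·√(pd − d²))² / d² = (0.3395 + 0.2202)² / 0.000484 ≈ 647.1, rounded up to 648. The stated 659 is within 3%. By enumeration at 659, McNemar power is 90.1% with continuity correction and 91.1% for the exact test. The 659 is therefore a sound McNemar figure, counted in cancers.

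**Step 2: how many discordant cancers.** The expected number of discordant pairs is 0.030·n, with 0.004·n in the smaller cell. The chance that at least one cell is empty is 0.996ⁿ + 0.974ⁿ − 0.970ⁿ. At n = 200 this is 0.4486 + 0.0052 − 0.0023 = 0.45.

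| Cancers | Discordant pairs expected | Smaller cell | Chance of an empty cell |
|---|---|---|---|
| 100 | 3 | 0.4 | 69% |
| 200 | 6 | 0.8 | 45% |
| 300 | 9 | 1.2 | 30% |
| 659 | 19.8 | 2.6 | 7% |

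**Step 3: what the Wald test does with such counts.** For discordant counts b and c, z = ln(b/c) / √(1/b + 1/c).

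- 6:0: the odds ratio is infinite and z has no usable value. The exact McNemar p is 2 × 0.5⁶ = 0.031. A conditional logistic fit stopped at a Wald p of 0.92; that figure depends on where the software stops iterating.
- 7:1: z = 1.946/1.069 = 1.82, p = 0.069.
- 8:1: z = 2.079/1.061 = 1.96, p = 0.0499.

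The Wald test therefore cannot reach p < 0.05 with fewer than 9 discordant pairs. The exact McNemar test can from 6.

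**Step 4: power at 0.4% and 2.6%.** Full enumeration over the number of discordant pairs and their split, two-sided 0.05, with an empty cell counted as non-significant for Wald:

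| Cancers | Wald | Exact McNemar | Mid-p McNemar |
|---|---|---|---|
| 100 | 0.1% | 3.3% | 8.6% |
| 200 | 6.1% | 25.0% | 37.6% |
| 300 | 25.9% | 49.3% | 60.7% |
| 400 | 49.8% | 67.2% | 75.7% |
| 659 | 85.8% | 91.1% | 93.9% |

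The mid-p gain does not come from an inflated error rate. With equal discordance of 1.5% each way and 200 cancers, the rejection rates are 3.0% for mid-p, 1.2% for exact and 0.4% for Wald.

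**Step 5: the benign outcome.** At 13.5% and 17.0% with 2026 individuals, power is 81.5% for Wald, for uncorrected McNemar and for mid-p, and 80.4% for exact McNemar. The choice of test makes no practical difference there.

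**The case against.** Several points on the other side are fair.

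- **The number of cancers is an assumption.** This stands. The chance of an empty cell falls from 69% at 100 cancers to 7% at 659, and the gap in power narrows with it. The shortfall at 659 does not depend on the assumption, since that is the plan's own number.
- **The discordance rates describe threshold against threshold.** They compare the LCP threshold with the Brock threshold, whereas two of the three LCP options are physician decisions set against recorded standard care. No rates are given for those, so sparsity there is inferred.
- **The counts will be reported anyway.** A reader could see a 6:0 split in the table. That limits the harm but does not repair the prescribed p-value and interval.

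A reader might also infer more than the document supports.

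- **That both primary outcomes need a new test.** Step 5 shows that the benign outcome does not.
- **That conditional logistic regression contradicts the McNemar sample size.** It does not: its score test for matched pairs is McNemar's test, and the Wald test is asymptotically equivalent. The fault is the Wald test in sparse cells.
- **That an odds ratio fails to answer Table 1.** The article promises numbers and percentages beside it, and McNemar's test also uses only discordant pairs. Making the paired difference the main effect measure is a preference.

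In the other direction, the remark in Statistical analysis about giving exact p-values might be taken as a commitment to an exact test. In context it concerns reporting p-values so that readers can judge significance.

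**Conclusion.** The point holds for the cancer-discharge outcome only. This is a stated choice of test that does not suit the data the plan itself anticipates, and an analysis plan that follows it would inherit the fault. At 0.4% and 2.6% discordance and an assumed 100 to 300 cancers, there is a 69% to 30% chance that the planned test gives no usable result. Its power is then well below that of an exact or mid-p test. At 659 cancers it reaches about 86% against the stated 90%.

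A reader might conclude that changing the test rescues the comparison. It does not: at 200 cancers, power is 25% with the exact test and 38% with mid-p. The small number of cancers is the larger limitation and remains.

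**What to change.** For cancer discharge, replace the Wald test with an exact or mid-p McNemar (exact conditional) test, named in advance. Report the conditional odds ratio with limits from the same method, so that the interval and p-value agree and a one-sided limit is still available when a cell is empty. A score-type confidence interval for the paired difference in percentages may be added as a supplement.

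Keep conditional logistic regression as the model if wished, and leave the benign outcome as it is. Restate the power for the chosen test at the number of cancers actually expected, and say plainly that it may be low.

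The cost is a change of wording, with no further data or patients. It should be made before the outcome data are examined.

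### The cancer-discharge primary is powered for McNemar's test but analysed with a Wald test, which fails when a discordant cell is empty and gives 86%, not 90%, power at the planned 659 cancers

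*Protocol article*

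**What the plan says.** The Sample size section bases the cancer-discharge objective on discordant pairs within the cancer group. It assumes that "the Brock model threshold (representing the standard of care) identified 0.4% of cancers for which the LCP threshold would have recommended discharge" and that "the LCP threshold correctly identified 2.6% of cancers for which the Brock model threshold would have recommended discharge". From these it concludes, "using McNemar’s test with 90% power and a significance level of 0.05, 659 participants would be needed". It adds that with 2000 participants "there is 90% power to detect a difference between the methods if the percentages were as small as 1.0% and 2.3%, respectively". The benign-nodule objective is sized on McNemar's test too: 17.0% against 13.5%, 80% power, 2026 individuals.

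The Statistical analysis section fixes a different test. For both primary objectives the differences "will be analysed using conditional logistic regression. Statistical significance will be assessed with a Wald test". Each outcome is to carry an odds ratio with a 95% confidence interval and "A two-sided p value". The closing remark about exact p values explains why no multiplicity correction is made. It is about printing the value and names no exact test.

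**The concern.** For matched pairs with one binary factor, conditional logistic regression depends only on the two discordant counts, b and c. McNemar's uncorrected test is the score test of this model, so the model agrees with the sample-size calculation. The difference lies in the choice of Wald within it. Score and Wald tests agree when both counts are large and part company when one is very small.

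The extreme case is an empty cell. The estimated odds ratio is then 0 or infinite, its standard error diverges, and the Wald p value drifts towards 1 however lopsided the data. If LCP discharged none of the cancers that standard care kept, the planned test could not show that advantage. The mirror-image result, a signal against LCP, would be hidden in the same way. This outcome counts missed cancers, the safety half of the primary objective, and the plan itself puts one discordant cell at 0.4% of cancers.

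**Working it through.** **Inputs (Sample size section).** Discordant probabilities among cancers p1 = 0.026 and p2 = 0.004; two-sided alpha 0.05; power 90%; stated n = 659. Hence pd = 0.026 + 0.004 = 0.030 and d = 0.026 − 0.004 = 0.022.

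**1. The plan's own figure.** The usual normal approximation for McNemar's test is

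n = [1.960·√pd + 1.282·√(pd − d²)]² / d² = [1.960·√0.030 + 1.282·√0.029516]² / 0.000484 = 647.1, so 648.

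This is 1.7% below 659, so the figure is essentially reproduced. For 1.0%/2.3% the formula gives 2048 against the stated 2000.

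**2. The Wald statistic.** z = |ln(c/b)| / √(1/b + 1/c), undefined if b or c is 0. Fitting the conditional model to 17 against 0 gave a standard error of about 67 and p = 0.87; uncorrected McNemar gives p = 0.00004. For 8 against 0, fitted Wald p values ran from 0.91 to 1.00 depending on the optimiser, whereas the exact p is 2 × 0.5⁸ = 0.0078.

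**3. Small but non-empty cells.** With 1 in the smaller cell, both Wald and exact McNemar need 8 in the other (Wald p = 0.0499, exact p = 0.039). With 2, both need 10. With 0, exact McNemar needs 6 and Wald never rejects. Against the exact test, the defect is therefore the empty cell.

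**4. Power at 659 cancers.** Expected counts are 659 × 0.004 = 2.6 and 659 × 0.026 = 17.1. The chance that the smaller cell is empty is 0.996⁶⁵⁹ = 7.1%. Power was found by full enumeration (discordant total binomial with n and 0.030, then split binomially), counting Wald as non-significant when a cell is empty:

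- Wald 85.8%
- McNemar, continuity-corrected 90.2%
- McNemar, exact 91.1%
- McNemar, mid-P 94.0%
- McNemar, uncorrected (score) 94.3%

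Wald reaches 90.0% at 730 cancers.

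**5. The plan's other power statements.** With 2000 cancers and 1.0%/2.3%, Wald gives 90.0% and uncorrected McNemar 90.3%. For the benign objective at 2026, Wald and uncorrected McNemar both give 81.5%.

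**6. Fewer cancers.** The documents give no prevalence; the Abstract says only that few such nodules are cancers. Assuming 5%, 10%, 15% or 20% of 2000, still at 0.4%/2.6%:

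| Cancers | At least one cell empty | Wald | Exact McNemar | Mid-P McNemar |
|---|---|---|---|---|
| 100 | 69% | 0.1% | 3% | 9% |
| 200 | 45% | 6% | 25% | 38% |
| 300 | 30% | 26% | 49% | 61% |
| 400 | 20% | 50% | 67% | 76% |

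With no true difference (1.5% in each cell) and 200 cancers, Wald rejects 0.4% of the time, mid-P 3.0% and uncorrected McNemar 4.7%.

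**The case against.** Several points on the other side stand.

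- **Size on the plan's own figures.** A reader might infer that an empty cell is what the plan expects. It is not: at 659 cancers a single-digit smaller cell is expected, while an empty one has a 7.1% chance. Wald works at the counts nearest expectation; 17 against 3 gives p = 0.006. The loss against the stated 90% is about 4 points.
- **The second 90% claim.** A reader might infer that Wald undercuts every power statement. It does not: 1.0%/2.3% at 2000 keeps 90.0%. That requires all 2000 patients to have cancer, which is a fault in the denominator and not in the test.
- **The low power at 100 to 400 cancers.** It is tempting to blame the Wald test for all of it. The cancer counts are assumed, and exact McNemar reaches only 3% to 67%. Most of the gap to 90% comes from setting per-cancer percentages against total recruitment, a separate problem.
- **Scope of the inputs.** The 0.4% and 2.6% compare two thresholds. The primary objective compares standard care with three LCP options, two of them physician decisions, for which no discordance rates are given. Sparsity there is plausible but not stated.
- **Direction and detail.** The Wald failure is conservative and does not inflate false positives; counts and percentages will be reported anyway. A sparse-data fallback may also sit in a full analysis plan that is not shown.

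The last point does not remove the concern. It rests on what the article does state: a named Wald test for an outcome sized on another test, with one very small discordant cell assumed.

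**Conclusion.** The concern holds, within limits. The named test for the cancer-discharge primary is not the one the sample size was computed for. It cannot return a finite odds ratio, a confidence interval or a significant result when a discordant cell is empty. On the plan's own assumptions this costs about 4 points of power (85.8% against 90%) and leaves a 7.1% chance of an unusable primary estimate. The benign primary is not affected.

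The consequence becomes serious only with far fewer than 659 cancers. That depends on a prevalence the documents do not give and on the 0.4%/2.6% rates carrying over. Under those assumptions Wald discards much of the little information available: at 200 cancers, 6% power against 25% (exact) or 38% (mid-P).

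**What to change.** For the cancer-discharge primary, replace the Wald test with the score (McNemar), exact McNemar or mid-P McNemar test, chosen before the data are seen. Report the conditional odds ratio with an exact or mid-P interval from the discordant pairs, which stays defined with an empty cell. For 8 against 0, the exact lower limit for the proportion is 0.025^(1/8) = 0.631, so the odds ratio runs from 0.631/0.369 = 1.71 to infinity. Restate the power in the Sample size section for the test adopted.

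The cost is a sentence in the analysis section, a revised power statement and a few lines of code; no new data are needed. Making the choice now avoids changing a primary analysis after an empty cell has been seen. It does not restore 90% power if cancers are few; that needs the denominator in the sample-size calculation to be addressed separately.

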#### Health economics analysis

The economic analysis will estimate the expected costs and expected quality-adjusted life years (QALYs) gained from standard care, LCP and LCP-guided care over patient lifetime from the perspective of the UK NHS. Incremental analyses will identify the most cost-effective permutation with exploratory analyses undertaken to determine the uncertainty around measures of cost-effectiveness. Costs will be calculated as quantities of resource use multiply by appropriate unit costs (eg, NHS Reference Costs) and will be specific to a year to be determined at time of analysis. A health economics analysis plan will be produced prior to undertaking the analysis at the end of the study patient follow-up period.

### Patient and public involvement

An extensive programme of patient and public involvement (PPI) input was arranged to provide input into the study objectives, design, materials and governance and planned to disseminate study results.

Specifically, a PPI representative, who sits on the Trial Management Group, provided input from study conception to developing study materials. This guidance and support will continue during the management and conduct of the study. An independent PPI contributor is a member of the trial steering committee. Further input was gathered from a group of PPI contributors selected from across the country with varying experiences of lung nodules, cancer or none from a patient and/or carer perspective during facilitated virtual workshops.

Input received to date has ranged from considerations of healthcare inequalities and other biases, awareness of AI generally and in healthcare, methods of and materials for participant recruitment and communication, and the design of any data collected during the study.

## Ethics and dissemination

This study has been reviewed and given a favourable opinion by the South Central—Oxford C Research Ethics Committee in UK (REC reference number: 22/SC/0142).

Given the study’s observational nature, we do not envisage any elevation to the harms or the risk of harm for patients. The sponsor and chief investigator have conducted a full risk assessment.

Patients will be asked to give their consent to participate in the study (including the analysis of standard-care CT scans, associated data collection and the healthcare economics assessment) by telephone or face to face when attending routine clinic appointments. No additional patient visits, scans or procedures are planned for the study. Patients not wishing to participate in the health economics assessment may still participate in the study’s CT imaging analysis.

The findings of this study will be shared with the funder (NHS Accelerated Access Collaborative). Results will be presented at academic and clinical conferences. The study will result in at least one peer-reviewed publication of the findings in an international medical journal.
